### Adverse events reporting and harms {22}

The PhD candidate will have thorough training on the operation of the machine, familiarise herself with the troubleshooting scheme, and closely monitor adverse effects during PEMF. In the event of a severe adverse reaction to the PEMF, it will be reported to the trial steering committee immediately. The participant will be removed from the trial and referred to the outpatient clinic at the Prince of Wales Hospital.

An independent auditor from the ethics committee will conduct the trial conduct annually. The trial steering group meet weekly to report research progress to the principal investigator. The principal investigator will complete a standardised progress report form for the ethics committee to review conduct annually during the trial period.

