In addition to PEMF, all participants will perform eccentric exercise. The first step is stretching exercises for the calf muscles. The stretching is a static stretch of the gastrocnemius (knee in extension) and soleus (knee in flexion). The participants are instructed to hold these for at least 30 s and repeat each exercise three times. There will be a 1-min rest between each stretch. Three sets of 10 repetitions of the eccentric exercises will be carried out once daily for 6 weeks. After 6 weeks, the participants will be instructed to carry out three sets of 10 repetitions three times per week for 6 more weeks. The intensity of the exercise should be such that pain, or discomfort, is experienced in the last set of 10 repetitions. Every session ended with the same static stretch exercise as in step 1. Suppose a participant is unable to complete three sets of 15 repetitions. In that case, the participant is instructed to start with fewer repetitions and sets (a minimum of 2 groups of 10) and progress to the total amount as able [7].

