### Criteria for discontinuing or modifying allocated interventions {11b}

The treatment will be stopped, and immediate care will be provided if any significant adverse effects happen during the treatment period, including a substantial increase in the severity of pain or discomfort.

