### Procedure for unblinding if needed {17b}

There will be unblinding of the participants and assessors if a severe adverse event occurs. The adverse event will be reported to the Joint Clinical Research Ethics Committee of the Chinese University of Hong Kong and the New Territories East Cluster of the Hospital Authority.

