### Interim analyses {21b}

An interim analysis will be performed on the primary endpoint when 20% of participants have completed the eight weeks of PEMF. The interim analysis ensures that there is no serious adverse event that happened during the study period.

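### The harms section ties adverse event monitoring to PEMF and to reactions to PEMF; this is narrower than three other sections, and no systematic collection is described for other causes or after week 8

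*Protocol article*

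**What the plan says.** The harms section of the protocol article, Adverse events reporting and harms {22}, gives the PhD candidate a monitoring task and a reporting rule: "closely monitor adverse effects during PEMF. In the event of a severe adverse reaction to the PEMF, it will be reported". The recipient of such a report is the steering committee, at once.

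Three other sections deal with the same subject in different terms:

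- Criteria for discontinuing or modifying allocated interventions {11b} stops treatment "if any significant adverse effects happen during the treatment period, including a substantial increase in the severity of pain or discomfort".
- Procedure for unblinding if needed {17b}: "There will be unblinding of the participants and assessors if a severe adverse event occurs". It continues: "The adverse event will be reported to the Joint Clinical Research Ethics Committee".
- Interim analyses {21b}: "The interim analysis ensures that there is no serious adverse event that happened during the study period".

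Both arms receive more than PEMF or sham. The Interventions section prescribes daily eccentric exercise for 6 weeks, at an intensity meant to bring on pain or discomfort in the last set. Then: "After 6 weeks, the participants will be instructed to carry out three sets of 10 repetitions three times per week for 6 more weeks". Table 2 schedules questionnaires, functional tests and ultrasound to 6 months, but has no adverse event row. Section {11c} has exercise compliance recorded at the PEMF visits and does not mention adverse events.

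**The concern.** What each arm receives is PEMF or sham together with exercise, and the exercise is painful by design. It runs to week 12, while PEMF ends at week 8. A rule that looks for adverse effects during PEMF, and reports to the steering committee only reactions to PEMF, does not match that package or the 6-month follow-up.

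The trial's own rationale makes this matter for the comparison. The Background section expects PEMF to relieve pain and so raise compliance with the exercise. If it does, exercise load may differ between arms, and so may any harm from that load. An event of that kind is not obviously a reaction to PEMF, and it may arise after the PEMF visits have stopped. The final report could then set benefit data to 6 months beside harms data gathered under a narrower and unclear rule.

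**Working it through.** **1. Scope of the four sections, side by side**

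| Section | Kind of event | Limited to PEMF? | Time window | Consequence |
|---|---|---|---|---|
| {22} | adverse effects; severe reaction | Yes | during PEMF | report to steering committee, removal from trial, referral |
| {11b} | significant adverse effect | No | treatment period | treatment stopped, immediate care |
| {17b} | severe event | No | none stated | unblinding, report to ethics committee |
| {21b} | serious event | No | study period | assurance drawn from the interim analysis |

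The degree of event, the attribution and the window all vary, and nothing in the article reconciles them. Sections {11b} and {17b} say what happens once an event is known. Neither says how events are to be found.

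**2. PEMF period (Interventions)**

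2 per week × 8 weeks = 16 sessions, which matches the stated 16.

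**3. Exercise (Interventions)**

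This assumes that exercise starts in the same week as PEMF.

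- Weeks 1–6: 7 × 6 = 42 sessions.
- Weeks 7–12: 3 × 6 = 18 sessions.
- Total: 42 + 18 = 60.
- By week 8: 42 + 3 × 2 = 48 (80%).
- After week 8: 3 × 4 = 12, and 12/60 = 20%.

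**4. Follow-up (Trial design, Table 2)**

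With 6 months taken as 26 weeks: 26 − 8 = 18 weeks after the PEMF course, and 18/26 = 69%. Two visits fall in this time, at 3 and 6 months. Neither has adverse event collection listed.

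**5. The interim assurance ({21b}, Sample size)**

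- Participants who have completed 8 weeks of PEMF: 0.20 × 40 = 8.
- One-sided 95% upper limit for the event rate when none of n participants has an event: 1 − 0.05^(1/n).
- n = 8: 1 − 0.05^(1/8) = 0.312, so about 31%.
- n = 40, for comparison: 1 − 0.05^(1/40) = 0.072, so about 7.2%.
- If the true rate were 5% (an illustrative value), the chance of seeing no event in 8 would be 0.95^8 = 0.663, so about 66%.

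An event-free interim look would thus say little about the event rate. The analysis is also described as being on the primary endpoint, which is VISA-A and not a safety measure.

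**The case against.** The strongest reply is that the harms section should not be read alone. Four stronger readings are tempting, and the document does not support them.

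- *Events are escalated only if they are reactions to PEMF.* Section {17b} sends any severe adverse event to the ethics committee, without limit of cause or time. Section {11b} acts on any significant adverse effect in the treatment period, including a marked rise in pain.
- *Harms from exercise go uncounted.* The Interventions section also has the PEMF operator monitor participants' clinical condition, and exercise compliance is recorded at the PEMF visits. As 48 of the 60 exercise sessions fall by week 8, many problems could come up there. The words in {22} may even mean the PEMF course and not the minutes under the device, so the 16 × 10 = 160 minutes of exposure is no measure of the chance to detect events. Pain scores and ultrasound are taken to 6 months in both arms, so worsening would show, although as efficacy data.
- *A blinded assessor cannot apply the trigger.* A suspected reaction to the assigned exposure, active or sham, can be recorded without knowing the allocation.
- *The interim assurance fails because of the collection rule.* It fails mainly on the number of participants, the timing and the endpoint, and better collection would not rescue it.

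It can also be said that a condensed article leaves adverse event forms to the full protocol. That is fair for form fields and coding. It does not cover a scope that the article states itself, and states differently in four places.

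**Conclusion.** The point holds as a badly fixed scope, not as an absence of safety reporting. Section {22} is narrower than {11b}, {17b} and {21b}. No systematic collection is described for events not attributed to PEMF. None is described for any event after week 8, which is about 18 of 26 weeks (69%) and includes 12 of 60 exercise sessions (20%). Followed as written, harms of the combined intervention cannot be compared reliably between arms over the period in which benefit is measured. It does not follow that the trial would report almost no harms, or that none could be seen: the document gives no basis for predicting either.

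The {21b} sentence is unsupported on its own account, because about 8 of 40 participants at 8 weeks cannot ensure anything about the whole study period.

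The figures assume that 6 months is 26 weeks, that exercise starts together with PEMF and is done as prescribed, and that the 20% refers to the planned 40.

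**What to change.** 1. Reconcile the terms and scope of {11b}, {17b}, {21b} and {22}: one set of definitions and one collection window, to 6 months.
2. At each PEMF or sham visit, and at the existing 3- and 6-month visits, ask the same open question in both arms about any adverse event since the last contact. Record events whatever the suspected cause, tabulate them by randomised arm, and add an adverse event row to Table 2.
3. Protect the later answers. Implementation {16c} discloses allocation to the PhD candidate and the orthopaedic surgeon once a participant's PEMF sessions are complete. Either collect later events on a form that participants fill in, or delay disclosure until the 6-month visit. Concealment mechanism {16b} withholds allocation from participants only until treatment ends, so the form helps only if they stay blinded too. Delay, applied to participants as well, is the cleaner choice.
4. Delete the {21b} sentence, or restate it as a review of the events recorded up to that look.

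Section {11b} stops treatment, while {22} removes the participant from the trial. These rules need to be reconciled with each other. No new clinical rule is proposed here.

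The cost is a protocol amendment, a short form at visits that already take place, a few minutes per visit and more minor events to list.

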### Sample size {14}

A minimum clinically significant difference is 16 points on the VISA-A scores based on the pilot study using VISA-A as the primary outcome in treating AT [18]. It was reported in a feasibility study using another conservative treatment, laser therapy as an adjunct treatment to eccentric exercise therapy for AT. A total of 20 participants were recruited and VISA-A was the primary outcome. Significant improvements were shown in both treatment groups in VISA-A [18]. The power calculation to detect the minimum clinically significant difference is conducted using the G Power programme at a type I error of 5%, power of 80% (correlation value, 0.03; pooled SD, 20.25). Twenty subjects per group are obtained to detect a significant difference in VISA-A among two groups if a two-way repeated-measures analysis of variance (ANOVA) is proposed. It is expected to have a 20% dropout rate. Thus, the final study sample size is 40 subjects in total [19].

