### Implementation {16c}

The chief engineer from Quantum TX performs the randomisation. The randomisation result is shared with the biostatistician at the Chinese University of Hong Kong. The orthopaedic surgeon and PhD candidate from CUHK recruit participants. The PhD candidate will complete the assessment and assigns participants to interventions. The randomisation results will only be disclosed to the orthopaedic surgeon and PhD candidate after the participants complete all PEMF sessions.

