### Methods in analysis to handle protocol non-adherence and any statistical methods to handle missing data {20c}

The intention-to-treat analysis will be used to include all study participants in the groups to which they are randomised, regardless of any departures from the original assigned group. The missing values will be estimated by multiple imputations with the assumption that values are missing at random.

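### Removing a participant from the trial after a severe reaction to PEMF would create outcome-related missing data that undermine the planned intention-to-treat analysis

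*Protocol article*

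**What the plan says.** All references are to the protocol article.

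- **Adverse events reporting and harms {22}.** The trigger and the consequence stand next to each other: "In the event of a severe adverse reaction to the PEMF, it will be reported to the trial steering committee immediately", and then "The participant will be removed from the trial and referred to the outpatient clinic at the Prince of Wales Hospital".
- **Criteria for discontinuing or modifying allocated interventions {11b}.** The rule here concerns the device treatment only: "The treatment will be stopped, and immediate care will be provided if any significant adverse effects happen during the treatment period". A marked rise in pain is named there as one such effect. Nothing is said about leaving the trial.
- **Methods for non-adherence and missing data {20c}.** Two commitments are made here: "The intention-to-treat analysis will be used to include all study participants in the groups to which they are randomised", and "The missing values will be estimated by multiple imputations with the assumption that values are missing at random". Section {20a} also commits to intention-to-treat.
- **Procedure for unblinding {17b}.** "There will be unblinding of the participants and assessors if a severe adverse event occurs". There is no condition on whether the event is related to PEMF or on who needs the allocation.
- **Implementation {16c}.** "The randomisation results will only be disclosed to the orthopaedic surgeon and PhD candidate after the participants complete all PEMF sessions".

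No section says whether outcomes are collected after a participant has been removed.

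**The concern.** Stopping the device and leaving the trial are different events for the analysis. A participant who stops PEMF but attends the remaining visits still supplies the outcome that intention-to-treat needs. A participant who leaves supplies nothing, and each later value has to be imputed.

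Under {22} the reason for leaving is a severe reaction to the treatment under test. If such reactions resemble the pain increase described in {11b}, the loss depends on something the primary outcome measures: under Outcomes {12}, pain is one of the three VISA-A domains. Missing at random then holds only if the data already recorded explain the later values. The worsening that led to removal may have occurred between visits and never been recorded.

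At stake is whether the comparison of VISA-A at the later visits reflects everyone randomised, or mainly those who tolerated their allocated treatment. A statistical analysis plan can vary the imputation, but it cannot recover outcomes that were never measured.

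**Working it through.** The plan gives no figure for this point, so there is none to reproduce. The check compares the sections and then gives an illustration.

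**Step 1: removal against discontinuation.** Section {11b} applies to significant adverse effects and ends treatment. Section {22} applies to a severe reaction to PEMF and ends participation. A severe reaction would ordinarily also count as a significant adverse effect, so both rules can apply to the same person, and they differ on whether that person stays in follow-up. In its ordinary sense, removal from the trial ends assessments, but the text does not say so.

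**Step 2: removal against the analysis.** Section {20c} keeps every randomised participant in the analysis and fills gaps by multiple imputation. A removed participant is therefore still analysed, but with imputed values after removal. Table 2 schedules outcomes at week 1, week 4, week 8, 3 months and 6 months. A reaction soon after the week 1 assessment would leave up to four of these five to impute. The only recorded outcomes would then predate the reaction.

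**Step 3: possible size.** Inputs:

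- Participants per arm: 20 (Trial design {8}, Sample size {14}).
- Target difference: "A minimum clinically significant difference is 16 points on the VISA-A scores" ({14}).
- Pooled SD: 20.25 ({14}).
- Number removed in an arm, k: not given; assumed 1 or 2.
- Gap between true and imputed VISA-A for a removed participant, G: not given; assumed 20 to 40 points.

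Shift in that arm's mean = (k / 20) × G.

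| k | G = 20 | G = 40 |
|---|---|---|
| 1 | 1/20 × 20 = 1.0 | 1/20 × 40 = 2.0 |
| 2 | 2/20 × 20 = 2.0 | 2/20 × 40 = 4.0 |

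Against the 16-point target this is 1/16 = 6% to 4/16 = 25%. Against the standard error of a simple two-group difference, 20.25 × √(2/20) = 6.4 points, it is 1/6.4 = 0.16 to 4/6.4 = 0.62 standard errors. Each removal also costs 1/20 = 5% of an arm's later outcomes.

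**Step 4: direction.** With kA removed from the active arm and kS from the sham arm, and the same G in both, the shift in the between-group difference is (kA − kS) / 20 × G. It is zero if removals are equal, favours PEMF if more active participants are removed, and works against PEMF if more sham participants are. The documents give no rate for either arm.

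**Step 5: unblinding, a separate matter.** Section {17b} reaches assessors for any severe event, whereas {22} removes only those with a severe reaction to PEMF. The people affected are therefore those with a severe event not attributed to PEMF, who stay and are measured by an unblinded assessor. Section {16c} in any case discloses allocation to the PhD candidate, who does the assessments, once PEMF sessions are complete. If that means each participant's own sessions, it precedes every 3- and 6-month visit. The extra exposure from {17b} then falls mainly on visits up to week 8.

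**The case against.** The strongest reply is that nothing conflicts. Section {20c} analyses everyone as randomised whatever departures occur, and {22} does not say that assessments stop. The first half stands: a reader might infer that the plan formally contradicts intention-to-treat, and it does not. The second half stands only in part. The wording leaves room for continued visits, but nothing provides for them, and the ordinary meaning points the other way.

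A reader might also infer that reactions to PEMF occur only in the active arm, so that the loss is one-sided and biases the result towards PEMF. The documents do not support this. Staff and participants are blinded during treatment, the sham uses the same device, and both arms do exercises meant to reach pain or discomfort. A reaction in a sham participant can therefore be attributed to PEMF and lead to removal. Nor does the plan give an imputation model from which to conclude that good-responder values would be imputed; multiple imputation normally also uses the participant's own earlier data.

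On size, {21a} calls the study low-risk, and the Interventions section reports only mild tingling or warmth in a few participants. Severe reactions may be very rare, and the illustrative shifts are below one standard error. This is fair and limits the weight of the point, but it is no reason to keep a rule that discards outcomes.

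On unblinding, VISA-A is completed by the participant, so assessor knowledge bears little on it; the assessor-read measures, such as the Öhberg grade and the lunge test, are more exposed. Each participant has a separate RFID card, so disclosing one allocation does not by itself reveal the others. The PhD candidate also monitors participants during treatment, so it cannot be assumed that the assessor never needs the allocation. All of this stands and makes unblinding the smaller issue.

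**Conclusion.** The point holds in limited form. Sections {11b} and {22} do not agree on whether a participant who reacts severely stays in follow-up. If removal ends assessments, the protocol creates missing outcomes for a reason related to treatment and probably to VISA-A. Intention-to-treat is then undermined, though not contradicted, and missing at random is doubtful for those values.

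Neither the direction nor the size of the bias can be derived from the documents. The 1 to 4 point shift in an arm mean rests wholly on the assumed 1 or 2 removals and the 20 to 40 point gap; with no severe reactions it is zero. The case for acting rests on the cheapness of the change and on the fact that lost outcomes cannot be recovered at the analysis stage.

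Event-driven unblinding under {17b} is separate and secondary. It neither conflicts with intention-to-treat nor causes imputation, and it matters only for participants who remain in follow-up.

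**What to change.** 1. Reconcile {11b} and {22}, leaving the clinical handling of reactions as it is. State that stopping treatment does not end follow-up, and that VISA-A and all other scheduled outcomes are collected at every remaining visit unless the participant withdraws consent. This costs one or two sentences and uses visits already in Table 2.
2. Separately, amend {17b} so that allocation after a severe event is disclosed only to those who need it for care, and the outcome assessor stays blinded where possible. For this to help at 3 and 6 months, the routine disclosure in {16c} must also wait until the last assessment, with {16b} and {17a} aligned. This costs a few words in each section and no added procedures.

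A sensitivity analysis that departs from missing at random would be a sensible companion. It may belong in the statistical analysis plan, which is not shown, so its absence here is not a fault.

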### Plans for communicating necessary protocol amendments to relevant parties (e.g. trial participants, ethical committees) {25}

The investigators will apply for protocol amendments to the ethics committee and should be approved by the ethics committee before implementation. Trial participants will be informed about the amendments to the protocol. The protocol changes will be published in the Trial Register.

## Dissemination plans {31a}

The early findings of the research will be presented at the Hong Kong Orthopaedic Association annual congress, the flagship event attended by all local orthopaedic surgeons. Final results will be presented at regional sports medicine conferences such as the Asia–Pacific Knee Arthroscopy and Sports Medicine (APKASS) Congress and published in a scientific peer-review journal. The funder does not pose any restrictions on the decision of publication.

## Discussion

AT is a clinical syndrome characterised by pain, swelling, and functional impairment, indicating a degenerative inflammatory process in the Achilles tendon. The overall incidence rate of AT was 2.45 per 1000 in the adult population between 21 and 60 years in their lifetime. It can affect athletes and non-athletes. Patients with AT commonly refer to persistent pain that may result in loss of function and activity cessation. The pathogenesis of tendinopathy can be described as failed healing of the diseased tendon. Failed recovery mainly refers to prolonged inflammation and failed resolution of the normal healing process. Furthermore, increased focal vascularity contributes to the clinical presentations of chronic tendon pain, stiffness, and weakness.

An increase in tendon thickness is often found in patients with AT. It could happen in either midportion or insertion of the Achilles tendon, which is caused by swelling of the affected area. Moreover, the ingrowth of new blood vessels into tendinopathic regions is often seen in ultrasound imaging. PEMF may reduce tendon inflammation, thus reducing tendon thickness and neovascularity. Tendon elasticity is measured by shear wave elastography (SWE). SWE could quantify soft tissue stiffness and provide an absolute value of the stiffness of the soft tissue. There may be an increase in tendon stiffness in patients with AT. This is because patients may reduce the level of activities because of pain associated with AT. PEMF may minimise tendon pain and facilitate the performance of the eccentric exercise. Thus, there may be a reduction in tendon elasticity.

This trial may demonstrate the effectiveness of PEMF in relieving pain, improving function, and restoring mechanical changes of the tendon in patients with AT. AT is a common clinical condition affecting both athletes and sedentary populations. Exercise prescription is used as a non-invasive therapy for patients with AT. However, some participants do not respond well to exercise therapy and conventional treatments. It is essential to investigate treatment adjuncts to improve rehabilitation outcomes for this group of patients.

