**Discussion:**

AT is a common clinical condition affecting athletes and sedentary populations. It is essential to investigate treatment adjuncts to improve rehabilitation outcomes for these patients. This trial may demonstrate the effectiveness of PEMF in relieving pain, improving function, and restoring mechanical changes of the tendon in participants with AT.

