##### Tendon elasticity

Shear wave elastography (SWE) quantifies soft tissue stiffness and provides an absolute value of tendon stiffness [12]. Once the optimal scan plane of the tendon is identified, the SWE function is activated. SWE is set at the penetration mode with the measurable range of stiffness standardised at 0–600 kPa. The SWE colour map (height × width: 1.4 cm × 1.3 cm) is placed just above the superior border of the calcaneum. Electrogram is obtained and stored when the colour signals become steady for five seconds. Tendon stiffness is measured with the stiffness measurement tool—Q-box. The circular measurement area (Q-box) is set to 2 mm in diameter, dependent on the tendon size, and covers the Achilles tendon without including other adjacent soft tissues. Q-box is placed at the middle part of the tendon within the SWE colour map. For each Q-box, the mean (in kPa) of the stiffness of the tendon is measured [14].

The ultrasound normalisation procedure for subjects with bilateral tendinopathy will be done by using the mean values measured in healthy individuals as stated in current evidence. The mean value of a healthy Achilles tendon was reported to be 5.3 mm [15]. No vessels appear throughout the Achilles tendon for a healthy tendon (Öhberg score 0) [16]. The range of tendon elasticity measured in shear wave elastography in men and women are 657.1–766.4667 kPa and 433.5677–782.8667 kPa, respectively [17].

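### The predicted fall in tendon stiffness cannot be read as restoration, because the 600 kPa measuring limit lies below the protocol's healthy male range and inside its female range

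*Protocol article*

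**What the plan says.** Two sections of the protocol article bear on this.

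- **Outcomes {12}, Tendon elasticity.** The instrument setting is fixed: "SWE is set at the penetration mode with the measurable range of stiffness standardised at 0–600 kPa". The recorded quantity is a stiffness: "For each Q-box, the mean (in kPa) of the stiffness of the tendon is measured". Reference values are then given for a particular use: "The ultrasound normalisation procedure for subjects with bilateral tendinopathy will be done by using the mean values measured in healthy individuals". For SWE they are: "The range of tendon elasticity measured in shear wave elastography in men and women are 657.1–766.4667 kPa and 433.5677–782.8667 kPa, respectively".
- **Discussion.** On disease: "There may be an increase in tendon stiffness in patients with AT". On treatment: "PEMF may minimise tendon pain and facilitate the performance of the eccentric exercise. Thus, there may be a reduction in tendon elasticity". This is the only place that gives SWE a direction. The paragraph after it, like the abstract, says the trial may show an effect in "restoring mechanical changes of the tendon in participants with AT" (the abstract's wording).

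SWE is scheduled at every assessment in Table 2, and the second aim under Objectives {7} includes the mechanical properties of the tendon. The Ultrasonographic outcomes section says both legs are scanned.

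**The concern.** The Discussion implies a diseased tendon that is stiffer than healthy and comes down towards normal. For that to be seen against the protocol's reference values, some readings must be able to lie above the healthy range. The stated scale does not appear to allow this.

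The wording adds to the difficulty. The kPa value is called stiffness in some sentences and elasticity in others, including the section title and the reference values. In ordinary usage lower elasticity could mean a stiffer tendon, so a reader meeting the prediction alone could take it either way.

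What is at stake is how the mechanical part of the second objective is interpreted. A significant fall in SWE could be presented as benefit on the strength of the Discussion, or as deterioration on the strength of the reference values, and a rise likewise. The protocol does not fix in advance which reading applies, so the choice could be made after the results are seen.

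**Working it through.** There is no calculated figure in the plan to reproduce. The check compares the stated limit with the stated reference ranges.

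**Inputs (all from Tendon elasticity)**
- Upper limit of the measurable range: 600 kPa
- Healthy men: 657.1 to 766.4667 kPa
- Healthy women: 433.5677 to 782.8667 kPa

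**Step 1. How much of each healthy range can be read?**
- Men: 657.1 − 600 = 57.1 kPa between the limit and the bottom of the range. Readable share: 0%. The limit is 600 / 657.1 = 91.3% of the lowest reference value.
- Women: (600 − 433.5677) / (782.8667 − 433.5677) = 166.4323 / 349.299 = 47.6%.

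**Step 2. Can a reading lie above the healthy range?**
- Men: it would have to exceed 766.5 kPa. Women: it would have to exceed 782.9 kPa. Both are above 600 kPa, so the answer is no in either sex.

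**Step 3. Which way does a fall move a reading?**
- Men: every reading below the limit is under 657.1 kPa, so any fall widens the gap. As an illustration (the 10% fall is assumed), 500 to 450 kPa takes the gap from 657.1 − 500 = 157.1 to 657.1 − 450 = 207.1 kPa.
- Women: a fall from 600 to 540 kPa stays inside the range. A fall that ends below 433.6 kPa (433.6 / 600 = 72.3% of the scale) leaves the range or moves further below it.
- In neither sex can a fall bring a reading down into the range from above.

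**Step 4. What does normalisation do in bilateral cases?**
The text refers to mean values but gives a range for each sex, so the divisor has to be assumed. The largest ratio obtainable is 600 divided by the reference:
- Men: 600 / 766.4667 = 0.78 to 600 / 657.1 = 0.91; with the range midpoint of 711.8 kPa, 0.84. It is below 1 for every choice within the range.
- Women: 600 / 782.8667 = 0.77 to 600 / 433.5677 = 1.38; with the midpoint of 608.2 kPa, 0.99.

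A man with bilateral disease therefore cannot reach a normalised value of 1, and a fall in his reading lowers the ratio further.

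**Step 5. Does a comparison with the other leg survive the limit?**
Let c be the unaffected tendon at baseline, and a0 and a1 the affected tendon before and after.
- If c is at or above 600 and both a0 and a1 are below it, the distance changes from c − a0 to c − a1. The change is a0 − a1, so the unknown c cancels.
- If the affected tendon is at the limit and c is below it, the distance is known only as at least 600 − c, but its direction is known.
- If both tendons are at the limit, the pair says nothing.

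**The case against.** The strongest reply is that the conflict is produced by an instrument setting. A male tendon truly at 657 kPa or more would saturate or be out of range. It would not be soft. Without the 600 kPa limit, the Discussion and the reference values could both be true. This stands: the conflict follows from the limit and is not a separate fault. A reader might infer that every measurable male tendon is softer than healthy, or that diseased tendons are, but the documents do not support either as a statement about tissue.

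Second, the reference values are stated for bilateral disease only. Both legs are scanned and bilateral cases have a special rule, so the other leg is the implied comparator in unilateral cases. For these a fall could be a move towards normal. This also stands and narrows the point. The two kinds of case may then be judged against different norms.

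Third, it is unclear whether the quoted ranges are limits for individuals or a range of averages. If averages, some healthy men could read below 657.1 kPa. The cited source is not at hand, so the comparison is with the reference as stated and not with every healthy man.

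Fourth, the Discussion is hedged throughout, SWE is not the primary outcome, and no rule says that a fall counts as benefit. A reader might infer that a fall *would* be reported as restoration. The text supports only that it *could* be. No one-sided test is specified either, so asking for a two-sided one would change nothing.

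Fifth, it may be said that the other leg cannot serve as a yardstick if healthy male tendons exceed the limit. This is only partly right: Step 5 shows that the direction is lost only when both tendons are at the limit.

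**Conclusion.** The concern holds in this limited form. The Discussion's expectation for SWE and the measuring range and reference values in the Tendon elasticity section are incompatible. None of the healthy male range and 47.6% of the female range can be read, and no reading in either sex can exceed normal. A fall in a male reading below the limit, or in a female reading ending below 433.6 kPa, moves away from the stated reference and could still be described as restoring tendon mechanics.

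This rests on taking the 0–600 kPa setting and the quoted ranges as printed, and on reading reduced elasticity as a lower kPa value, which the context supports. The conflict is direct for bilateral cases. In unilateral cases it affects the interpretation only where these values are used as the picture of a healthy tendon.

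The point should be settled before analysis, because it decides what the trial can conclude about mechanical properties. It does not touch the VISA-A primary outcome.

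**What to change.** 1. Reconcile the measurable range with the reference values in the Tendon elasticity section, and do not normalise to a reference outside the measurable range.
2. Use one name throughout: *tendon stiffness (kPa, higher = stiffer)*.
3. In the Discussion, remove the predicted reduction as a marker of benefit. Renaming alone does not settle the interpretation, so the next item is needed as well.
4. Allow a restoration conclusion for SWE only if, in unilateral cases, the affected tendon moves closer in the active arm than in the sham arm to the participant's own unaffected tendon at baseline. Flag readings at 600 kPa as censored, and treat pairs with both tendons at the limit as uninformative.

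The cost is wording in two sections and one derived variable from bilateral scans already planned. The downside is that a restoration claim becomes harder to make, and bilateral cases do not contribute to it, which reduces the number available from a trial of 40.
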